## Abstract

**Background:**

Juvenile idiopathic arthritis (JIA) is one of the most common types of arthritis among children. According to JIA guidelines for physical activity (PA), structured PA interventions led to improved health outcomes. However, many PA programs, such as yoga and aerobic dance, have not been studied in this population despite being popular among youth. Web-based PA programs could provide patients with accessible and affordable interventions.

**Objective:**

The primary aims of the proposed pilot randomized controlled trial (RCT) are to examine (1) the feasibility of conducting a full-scale RCT to evaluate the effectiveness of two popular types of PA: a yoga training program and an aerobic dance training program, in female adolescents (aged 13-18 years) with JIA compared with an electronic pamphlet control group; and (2) the acceptability of these interventions.

**Methods:**

A three-arm prospective randomized open-label study with a parallel group design will be used. A total of 25 female adolescents with JIA who have pain will be randomized in a ratio of 2:2:1 to one of the 3 groups: (1) online yoga training program (group A: n=10); (2) online aerobic dance training program (group B: n=10); and (3) electronic pamphlet control group (group C: n=5). Participants in groups A and B will complete 3 individual 1-hour sessions per week using online exercise videos, as well as a 1-hour virtual group session per week using a videoconferencing platform for 12 weeks. Participants from all groups will have access to an electronic educational pamphlet on PA for arthritis developed by the Arthritis Society. All participants will also take part in weekly online consultations with a research coordinator and discussions on Facebook with participants from their own group. Feasibility (ie, recruitment rate, self-reported adherence to the interventions, dropout rates, and percentage of missing data), acceptability, and usability of Facebook and the videoconferencing platform will be assessed at the end of the program. Pain intensity, participation in general PA, morning stiffness, functional status, fatigue, self-efficacy, patient global assessment, disease activity, and adverse events will be assessed using self-administered electronic surveys at baseline and then weekly until the end of the 12-week program.

**Results:**

This pilot RCT has been funded by the Arthritis Health Professions Association. This protocol was approved by the Children’s Hospital of Eastern Ontario Research Ethics Board (#17/08X). As of May 11, 2020, recruitment and data collection have not started.

**Conclusions:**

To our knowledge, this is the first study to evaluate the effectiveness of yoga and aerobic dance as pain management interventions for female adolescents with JIA. The use of online programs to disseminate these 2 PA interventions may facilitate access to alternative methods of pain management. This study can lead to a full-scale RCT.

**International Registered Report Identifier (IRRID):**

PRR1-10.2196/12823

## Introduction

### Juvenile Idiopathic Arthritis and Physical Activity

Juvenile idiopathic arthritis (JIA) is one of the most common types of arthritis among children [1-3]. Symptoms, which include joint pain, stiffness, swelling, and fatigue [4-6], can significantly affect most children’s health-related quality of life (HRQOL). Although adolescents in the general population spend on average 57% of their time engaging in sedentary behavior after school [7], youths with JIA tend to be less active than their healthy peers and meet the national recommendations for physical activity (PA) less often [8]. Physical inactivity associated with JIA may lead to poor bone mineral density, increased fatigue, decreased muscle strength, reduced cardiorespiratory fitness capacity, reduced endurance, loss of functional independence, and diminished quality of life [9-13]. Prolonged physical inactivity may increase the risk of coronary heart disease, diabetes, hypertension, and obesity in adolescents with JIA [14,15]. It is important to help ensure that these symptoms are managed and to promote PA to reduce these long-term consequences [16]. According to recent guidelines for PA in JIA based on a systematic review of the literature [16], structured PA interventions compared with a control were, in general, effective in the self-management of JIA for numerous health outcomes, such as a reduced number of active joints [17,18], diminished pain intensity [19], increased joint range of motion [18,19], increased muscle strength [20,21], improved functional status [19,22], and enhanced quality of life [19,22].

### Yoga and Aerobic Dance

Many specific PA programs, such as yoga and aerobic dance, have not yet been studied in this population [16] despite being recommended by several rheumatology organizations such as the Arthritis Foundation and being popular among youths, especially females [23,24]. The fact that yoga and aerobic dance appeal to female adolescents may encourage them to adopt and adhere to these programs longer [23-25].

Yoga has been found to be beneficial for adults of both sexes with rheumatoid arthritis (RA) in reducing pain, pain disability, and swollen and tender joints, increasing functional status and enhancing quality of life, general health, and vitality as well as self-efficacy regarding pain [26-29]. Although no randomized controlled trial (RCT) has demonstrated the effectiveness of yoga in the management of JIA, a single-case design study found yoga (practiced by following a DVD) to be safe and feasible for 2 female adolescents with JIA [25].

There are currently no RCTs on the effectiveness of structured aerobic dance programs for the management of JIA, although it was found that a Zumba program improved the quality of life (*P*<.001) and aerobic cardiovascular capacity (*P*<.001) of female college students aged between 19 and 23 years from the general population [30]. Other studies showed that a dance intervention improved self-rated health and reduced emotional distress among adolescent girls with internalizing problems (eg, depressed mood, low self-worth) [24,31].

### Disseminating Physical Activity Through Information and Communication Technologies

Although PA interventions may be effective, there is a need to disseminate them to patients in a feasible and cost-effective way. A recent systematic review [32] revealed that information and communication technologies (ICTs) such as a Facebook offer for an exciting dissemination strategy by providing users continuous self-monitoring and self-management as well as real time feedback and information exchange [33-36]. ICTs are particularly appealing to young people as they enhance accessibility and acceptability [34,37-39]. Although ICTs have been successfully used to engage the youth, change behaviors, and provide support and education [32,39-42], few RCTs have used them to deliver information on health-related interventions [43-47]. One study successfully delivered videos of effective PA interventions to adults with arthritis via Facebook [48]. Facebook is one of the most popular and frequently used social media platforms among adolescents [34,38,39,41,49,50]. It has many features that can collect data on content popularity and audience response [51,52]. However, a similar RCT has not been conducted in JIA. Given the high prevalence of JIA among females (ie*,* 2-4 times more than males) [2,53,54], there is a need to disseminate potentially effective PA activities such as yoga and aerobic dance to this population in an accessible and affordable manner.

### Objectives

The primary objectives of the proposed single-blind three-arm pilot RCT with a parallel group will be to examine (1) the feasibility of a 12-week full-effectiveness trial of two popular types of PA and an electronic pamphlet control group: group A: an online yoga training program and a PA electronic educational pamphlet; group B: an online aerobic dance training program and a PA electronic educational pamphlet; group C: an electronic pamphlet control group (PA electronic educational pamphlet) postintervention; and (2) the acceptability of the yoga and aerobic dance PA interventions. The secondary objective of this pilot RCT will be to examine the initial effectiveness of a yoga training program (group A) and an aerobic dance training program (group B) on pain intensity, participation in PA, morning stiffness, functional status, self-efficacy, fatigue, patient global assessment, disease activity, and adverse events in female adolescents (aged 13 to 18 years) with JIA compared with an electronic pamphlet control group (group C) postintervention.

## Methods

The following methodology is in full agreement with the Standard Protocol Items for Randomized Trials recommendations for RCTs [55-57] to ensure methodological rigor.

### Study Design

This study will use a three-arm prospective randomized open-label study. Participants will be randomized to one of the 3 following groups in a ratio of 2:2:1: group A: an online yoga training program (and a PA electronic educational pamphlet; n=10); group B: an online aerobic dance training program (and a PA electronic educational pamphlet; n=10); and group C: an electronic pamphlet control group (PA electronic educational pamphlet; n=5). The total intervention period will be of 12 consecutive weeks. The frequency and duration of the interventions are based on other trials of yoga and PA interventions in pediatric and adult rheumatology [18,20,22,26,58]. As this pilot RCT involves physical interventions (ie*,* yoga and aerobic dance training programs), the participants and the research coordinator administering the program will not be blinded. However, the use of anonymous online self-reported questionnaires administered at baseline and postintervention will reduce potential detection bias. With training and standard operating procedures in place, it is anticipated that any performance bias due to not blinding will be minimized.

### Study Population

Participants will be included in the study based on the following criteria: (1) female adolescents aged between 13 and 18 years; (2) diagnosis of JIA by a rheumatologist according to the International League of Associations for Rheumatology (ILAR) criteria; (3) absence of serious comorbidities or chronic diseases or of chronic pain that is unrelated to JIA (eg*,* cancer, fibromyalgia), which may impact the ability to understand and use the exercise program or complete outcome assessments (as determined by the treating rheumatologist); (4) presence of arthritis-related pain during regular activities of at least 30 on a 100-mm visual analog scale (VAS) in the past month; (5) JIA-specific medication regimen not expected to change during the study period; (6) self-reported as not meeting Health Canada’s and American College of Sports Medicine’s guidelines for PA (<60 minutes of moderate-to-vigorous PA per day) and not using physical interventions/treatments other than medication prescribed for JIA pain relief or over-the-counter medication; (7) capable of using and accessing the internet weekly for the study duration; (8) no contraindications to exercise (according to the treating rheumatologist); and (9) ability to understand English. Participants will be excluded from the study if they do not meet the inclusion criteria.

### Interventions

#### Group A

Participants assigned to this group will be invited to complete a yoga training program. The yoga training program, an evidence-based educational program, is a structured low-intensity Vishwas Raj [26]. This yoga program consists of stretching, strengthening, meditation, and deep breathing and has been shown to be acceptable and effective among adults with RA. Participants will be asked to complete 3 individual 1-hour sessions per week for 12 consecutive weeks by watching a previously filmed session led by a qualified yoga instructor and posted on Facebook. They will also take part in a 1-hour virtual group session per week using a video-conferencing platform. Participants will also participate in weekly online consultations with a research coordinator and discussions on Facebook with other participants in group A. Finally, participants will receive an electronic pamphlet on physical exercise developed by the Arthritis Society. The electronic pamphlet, which groups B and C will also receive, explains how PA can help manage arthritis. It includes valuable tips and a detailed list of the various types of PA and exercises.

#### Group B

Participants assigned to this group will receive the electronic pamphlet on physical exercise and will be invited to complete an aerobic dance program. The aerobic dance program is a low-to-moderate intensity–level program and will also use a video. The video, adapted for youths with JIA, was developed with feedback from a JIA patient with experience in aerobic dance and a physiotherapist with experience in pediatric rheumatology. The aerobic dance program will have the same characteristics in terms of frequency, total number of sessions, and total duration as the yoga program (ie*,* three 1-hour individual sessions and one 1-hour virtual group session per week for 12 weeks). Participants will also participate in weekly online consultations with a research coordinator and discussions on Facebook with other participants in group B.

#### Group C

Participants assigned to this group will receive the electronic pamphlet on physical exercise and will participate in weekly online consultations with a research coordinator to discuss their use of all types of PA in the past, the electronic pamphlet on PA, and their future use of PA. They will also participate in discussions on Facebook with other participants in group C. After the completion of the study, the yoga and aerobic dance training videos will be available to all participants, including those in the control group. In recruitment documents, this group will be termed the electronic pamphlet group.

### Outcomes

The feasibility of a full trial will be monitored throughout the study (eg*,* randomization, recruitment and retention of participants, data collection, and self-reported adherence). The acceptability of the interventions will be assessed using online questionnaires at the end of the study.

Clinical outcomes will be evaluated at baseline, weekly, and postintervention (at 12 weeks) through the use of online questionnaires in REDCap (Vanderbilt University). At baseline, pain intensity, functional status, fatigue, and self-efficacy will be assessed. Pain intensity and fatigue will be monitored weekly. Finally, all of these outcomes as well as the patient’s global assessment will be assessed postintervention. Outcomes were selected based on a JIA core set of outcomes to assess in trials [59]. Outcomes that were found to be essential include pain, functional status, patients’ overall well-being (global assessment), joint inflammation signs, and adverse events [59]. Other outcomes that were found to be important but not essential include fatigue, joint stiffness, and PA [59]. Other outcomes need more research to be endorsed, such as coping with the illness, which is related to self-efficacy [59].

### Recruitment

The recruitment of a convenience sample of 25 participants (in a ratio of 2:2:1) will be performed at the Children’s Hospital of Eastern Ontario (CHEO) Pediatric Rheumatology Clinic. Rheumatologists at the CHEO Rheumatology Clinic will be provided with the inclusion and exclusion criteria for the study. During regular scheduled visits, treating rheumatologists will identify and direct eligible participants with JIA (and their parents) to the research coordinator who will explain the study in detail. Eligible participants will be invited to complete a screening questionnaire to ensure that they meet the study selection criteria before central randomization. If eligible, participants will be asked to sign either a consent form if they are able to consent or an assent form and their parent/guardian will be asked to sign a consent form. They will also complete a questionnaire that will gather sociodemographic and medical information as well as a validated questionnaire on participation in PA. They will also be asked about their preference in terms of PA.

### Participant Allocation

Once informed consent is obtained, participants will be randomly assigned to one of the 3 groups using the central randomization scheme [60] and based on a sequence of computer-generated random numbers using a blocking factor (randomly varying between 6 and 9). The central stratified randomization process will be based on age (between 13 and 15 years and between 16 and 18 years).

Before running the randomization program, the data manager will document the participant’s initials (first and last names) and date of birth (month and year). After running the program, the data manager will prepare sealed opaque envelopes with the group allocation and study ID number for each patient and will provide it to the research coordinator. Participants will open the sealed opaque envelope containing their group assignment and a confidential link to access their Facebook group page where further instructions can be found. The research coordinator will explain the procedures related to the group assigned and will ask participants to indicate their availability for an initial individual online consultation as well as for virtual group sessions. Participants will be asked not to change their usual level of PA during the study except for following the program to which they were assigned.

At the clinic, participants will complete a questionnaire that will gather the following information:

Sociodemographic information: partial date of birth (month/year), age, gender, ability to understand English, and ability to use and access the internet weekly for the study duration.Medical information: diagnosis, partial date of diagnosis (month/year), disease duration, presence of serious chronic diseases (eg, cancer or other illnesses) or cognitive impairments, presence of contraindications to exercise (as determined by the treating rheumatologist), current use of JIA-specific medication, anticipated change in JIA-specific medication in the next 12 weeks, and use of physical interventions/treatments other than the prescribed medication for JIA pain relief and pain level when performing regular activities. A chart review will help verify this information.PA information: the amount of PA performed weekly using a validated exercise log [61] and preferences in terms of PA (eg, yoga, Zumba, or other types).

At baseline, all the participants will be asked to do the following:

Create a new Facebook account: All participants will be asked to create an account specifically for the study and select a username that is meaningful to them but does not contain their first or last name, allowing them to remain anonymous.Access the group Facebook page: All participants will be invited to access the link to their group Facebook page, which they will be provided during their group assignment. Participants will be invited to follow the REDCap link provided on the Facebook page and answer baseline questionnaires about their participation in PA, pain, morning stiffness, functional status, fatigue, self-efficacy, and patient global assessment. This will take about 20 to 30 min to complete. The Facebook page will also contain the electronic pamphlet on PA (for all groups), the exercise videos (for groups A and B), and other information.

Following these steps, participants will be asked to complete the training program:

Groups A and B:

Participants will be invited via Facebook and email to attend an individual online consultation with the research coordinator using a videoconferencing platform. During this consultation, participants can ask questions related to their group assignment, voice their concerns, and establish a plan of action. For the remainder of the study duration, participants will be encouraged to attend, when possible, individual 10-minute online consultations weekly. During these consultations, participants can provide their feedback and discuss their use of the PA program as well as facilitators and barriers to participating. Private meetings are less difficult to schedule than group meetings and provide greater privacy. They may also be more motivating and less intimidating for participants who may feel their voice really matters and has an impact.For the study duration, participants will be asked to complete 3 individual exercise sessions as well as 1 virtual group session each week. The links to the videos will be posted on Facebook and sent by email for participants to use for their individual exercise sessions. For group sessions, the videoconferencing platform link will be posted on Facebook and sent to participants via email. Virtual group sessions will help ensure that they perform the exercises that they observe in the video safely and that they do not hurt themselves. They will also be able to see other participants and be seen if they wish, which will be a motivating factor to perform the PA. A schedule of virtual group sessions offered in the morning or afternoon will be posted on the Facebook group page or sent by email.Participants will be asked to record their PA using a validated exercise log [61] as well as their pain intensity and fatigue by completing a brief online questionnaire that regroups valid instruments on a weekly basis. They will be reminded to do so via Facebook, email, and during their online consultations.

Group C: Participants will be invited via Facebook and email to attend an individual online consultation with the research coordinator using a video-conferencing platform. During this consultation, participants can ask questions related to their group assignment, voice their concerns, and discuss PA in general and their plan for PA in the future. They will also be invited to consult the electronic pamphlet on PA each week. For the remainder of the study duration, participants will be encouraged to attend, when possible, individual weekly 10-min online consultations. During these consultations, participants can discuss their use of PA, as well as facilitators and barriers to participating in PA. Participants will be asked to record their PA using a validated exercise log [61] as well as their pain intensity and fatigue by completing a brief electronic questionnaire that regroups valid instruments on a weekly basis.

Throughout the study, the Facebook pages will provide a means of communication for participants who will be able to share their experiences, post comments on the videos, and ask questions of each other and the research coordinator. Access to Facebook group pages will be restricted to study participants. Adolescents who cannot or do not want (or are not granted parental permission) to access Facebook will be given a link to the CHEO webpage that will contain information related to the study and their group. However, they will not be able to interact (ie*,* leave comments or questions) using this platform.

At 6 and 12 weeks, all participants will be asked to complete online questionnaires about the program that they were allocated to as well as the acceptability of Facebook to deliver PA programs. They will also be asked if they used any other PA during the study. They will also complete online questionnaires assessing their pain intensity, functional status, fatigue, self-efficacy, and well-being (using a patient global assessment). This will take about 20 to 30 minutes to complete.

As a compensation for the time given by participants, they will receive a US $21.40 gift certificate for completing baseline questionnaires and a US $21.40 gift certificate for completing postintervention questionnaires. They will also receive a personalized certificate of participation (community hours for school).

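### Randomly varying block sizes of 6 to 9 do not fit the 2:2:1 ratio: no block of those sizes can hold it exactly

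*Protocol article*

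**What the plan says.** The ratio is stated consistently. Study Design says: "Participants will be randomized to one of the 3 following groups in a ratio of 2:2:1". The Recruitment section repeats it with the total: "The recruitment of a convenience sample of 25 participants (in a ratio of 2:2:1"). The Methods paragraph of the abstract gives the arm sizes: "online yoga training program (group A: n=10"), "online aerobic dance training program (group B: n=10") and "electronic pamphlet control group (group C: n=5").

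The blocking rule appears once, under Participant Allocation. The list is computer-generated, "using a blocking factor (randomly varying between 6 and 9"). The same section adds stratification: "The central stratified randomization process will be based on age (between 13 and 15 years and between 16 and 18 years"). Each of the two strata therefore needs its own sequence of blocks.

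Nothing in the article describes unequal or padded blocks, or any other device that would let these block sizes carry a 2:2:1 ratio.

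**The concern.** Blocking exists to hold the allocation ratio at the end of every block. The article fixes both the ratio and the range of block sizes, and the two do not match. This is not a detail left to a fuller document: both rules are stated, and they conflict as stated.

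Whoever generates the list must choose a way round the conflict, and the article does not say which. The choice matters in two ways. Treating 6 and 9 as equal-allocation blocks would move participants from the two exercise arms, whose acceptability is a primary objective, into the control arm. Rounding within blocks would keep the average shares but loosen the balance, in a trial where one arm has only 5 planned participants. Dropouts are to be reported by group, and the randomization process is itself listed as a feasibility measure, so the rule should be executable as written.

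**Working it through.** **Inputs.** Total 25, ratio 2:2:1 and arms 10/10/5 (abstract, Study Design, Recruitment). Block sizes 6 to 9 and two age strata (Participant Allocation).

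**The plan's own figure.** 25 × 2/5 = 10, 25 × 2/5 = 10 and 25 × 1/5 = 5. The total, the ratio and the arm sizes agree with one another.

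**Divisibility.** A block of size b holds 2:2:1 exactly if 2b/5 and b/5 are whole numbers, that is, if b is a multiple of 5. It holds 1:1:1 if b is a multiple of 3.

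| Block size | 2:2:1 content (A/B/C) | Holds 2:2:1? | Holds 1:1:1? |
|---|---|---|---|
| 6 | 2.4 / 2.4 / 1.2 | no | yes (2/2/2) |
| 7 | 2.8 / 2.8 / 1.4 | no | no |
| 8 | 3.2 / 3.2 / 1.6 | no | no |
| 9 | 3.6 / 3.6 / 1.8 | no | yes (3/3/3) |
| 5 | 2 / 2 / 1 | yes | no |
| 10 | 4 / 4 / 2 | yes | no |

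**What each workaround gives.** Each scheme was simulated with 20,000 lists of 25 participants in two strata. The article does not give the age mix, so each participant is assumed equally likely to fall in either stratum.

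- *Sizes 6 and 9 only, run as 1:1:1.* The mean is 8.3/8.3/8.3 (25/3 = 8.33). Controls fall between 6 and 11 in practically every list. Exactly 10/10/5 occurs in 0.02% of lists or fewer.
- *Sizes 6 to 9, controls rounded to the nearest whole number.* Controls per block are 1, 1, 2 and 2. One block of each size holds 6 controls in 6 + 7 + 8 + 9 = 30 participants, or 20%. A and B share the other 24, with the odd place in sizes 6 and 9 assigned at random. The mean is close to 10/10/5. Controls range from 2 to 8 and lie between 4 and 6 in 93% of lists. Exactly 10/10/5 occurs in about 18%. A and B differ by 2 or more in about 45%.
- *Sizes 6 to 9, each block a 2/2/1 core plus random extras.* The mean is close to 10/10/5, with an exact hit in about 13%.
- *Blocks of 5.* The mean is 10/10/5, controls are always 4 to 6, and exactly 10/10/5 occurs in about 45%. A and B differ by 2 or more in about 27%.
- *Blocks of 5 and 10 mixed.* The mean is 10/10/5, controls are 4 to 6 in about 98%, and exactly 10/10/5 occurs in about 32%.

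With blocks of 5, the total is always 10/10/5 if both stratum counts are multiples of 5, for example 10 and 15. Otherwise the last block in a stratum is incomplete and the total can drift.

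**The case against.** A reader might go further and conclude that the list cannot deliver 10/10/5 at all, or that the ratio and the blocking rule cannot both be implemented. The documents do not support that. Exactness within each block is a stronger requirement than the ratio over the whole list. Ignoring strata, uneven blocks of 8 (3/3/2), 8 (3/3/2) and 9 (4/4/1) sum to 10/10/5. Nearest-integer rounding keeps the average shares essentially at 2:2:1. This objection stands: what is lost is exact control within blocks and some precision of balance, not the ratio on average.

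A reader might also infer that the block sizes were carried over from a 1:1:1 design, and so expect about 8 per arm. Sizes 6 and 9 do fit that ratio, but 7 and 8 do not, and every statement of the ratio in the article is 2:2:1. The 1:1:1 figures show one possible outcome and are not a description of the plan.

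It can further be said that the stakes are small. The primary objectives are feasibility and acceptability, the sample-size section contains no calculation that depends on 10/10/5, feasibility denominators will be the numbers actually randomized, and randomization is valid whatever split results. All of that stands and limits the severity. It does not remove the mismatch, because no described algorithm reconciles the two rules.

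Finally, multiples of 5 do not guarantee 10/10/5 either. That is correct, and the revised text should say so.

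**Conclusion.** The point holds in this form: block sizes of 6 to 9 do not fit a 2:2:1 ratio, so the list as specified cannot hold the ratio within blocks by design. The divisibility result needs no assumption beyond ordinary permuted blocks. The size of the effect depends on an undocumented choice. It runs from looser balance around the right average (nearest rounding) to arms averaging about 8.3 each (6 and 9 used as 1:1:1). The simulated percentages rest on equal-probability strata and would shift with another age mix.

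It should be fixed before first randomization. It does not threaten the validity of the randomization or any powered comparison.

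**What to change.** Before the list is generated, replace the range 6 to 9 in Participant Allocation with block sizes that are multiples of 5, for example 5 and 10 randomly varied, within each age stratum. Add that 10/10/5 is the expected split and is not guaranteed, because the last block in a stratum may be incomplete. If an uneven-block algorithm was intended, describing it would also resolve the conflict, at the price of the looser balance shown above.

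The cost is one line of text and, if a list already exists, a new one. The Results section says recruitment had not begun as of May 11, 2020, so on that date nothing would have had to be undone. There is a small trade-off. Blocks of 5 alone are more predictable in an open-label trial, while mixing in blocks of 10 leaves slightly more imbalance at the end (exactly 10/10/5 in about 32% of lists instead of 45%).
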